### 2.5. Data Collection (Phase V)

Data collection for this study will be organized around the intervention. First, students and teachers will complete quantitative questionnaires. These will be given at two points, (1) before the intervention (baseline) and (2) after the two sessions (post-intervention follow-up). Second, fidelity and implementation-related data will be collected during the intervention (session logs and observational checklists). These will be collected between the two sessions. Third, qualitative data will be collected after the intervention. This will involve semi-structured interviews and focus groups with participants (students and teachers). Moreover, team-members (other than MTs) will collect the data at each phase of the intervention. As stated, both quantitative (questionnaires) and qualitative data (interviews and FGs) will be collected for this study. The questionnaires will be developed for this and will consist of closed and open questions presented in a structured format. Specifically, close-ended questions will be either Likert-type (rated 1-almost never to 5-almost always) or dichotomous (yes or no). Each question will yield a score, and these scores will be summed for a total. Higher total scores will indicate a greater level of the measured variable. The estimated time for completing both the questionnaires and the interview is approximately 60 min.

#### 2.5.1. Quantitative Data Collection Students

Quantitative data from students will be collected using two structured, self-administered questionnaires developed for this study at two timepoints, baseline (before the delivery of the sessions) and follow-up (after the delivery of the two sessions) (Table 4). The baseline questionnaire will assess socio-demographic characteristics, family environment, cigarette use, e-cigarette use, nicotine pouch use, exposure to secondhand smoke, exposure to air pollution, respiratory symptoms, and the impact these factors have on students’ productivity. Tobacco-related sections will include detailed measures of ever-use of tobacco products, past-30-day use of tobacco products, tobacco offers received from peers, susceptibility and curiosity towards tobacco use, intentions (to initiate smoking, quit smoking or try smoking), and perceived harm from three product categories: cigarettes, e-cigarettes, and nicotine pouches. The follow-up questionnaire will include 50 items. This questionnaire will reassess tobacco use and susceptibility measures to allow for pre- and post-intervention comparisons. There will be a section which will assess refusal capacity, the perceived usefulness of the two sessions, and students’ reactions to tobacco offers. For both questionnaires, students will rate their agreement on a four-point Likert scale, ranging from 1 (probably not) to 4 (probably yes).

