Several primary care behavioral interventions, including education or brief counseling, have been implemented to reduce TU in low-, middle- and high-income countries that target adolescents with a primary focus on smoking cessation [20,21], yet these measures have shown limited long-term success [21,22,23,24]. However, beyond the importance of designing and implementing interventions to help smokers quit, it is crucial to work towards preventing the initiation of young people into this addiction. The focus of prevention programs should be on educating adolescents who have never smoked to increase their knowledge, develop positive attitudes towards not smoking, build self-confidence, and give them the skills to decline the use of tobacco products. Additionally, programs should prevent adolescents already experimenting with TU from continuing [25].

In this context, schools present an excellent opportunity to introduce healthy lifestyle programs, such as those aimed at preventing TU, because they have access to a large and diverse student population at a key developmental stage, at a location where these students spend much of their day. Furthermore, these settings have proven useful for facilitating changes in numerous health behaviors [26]. School-based programs, such as the INTENT program from the University of Leeds in the UK [27], use “Implementation Intentions” (specific “if…then” plans) and have shown promise in Randomized Clinical Trials by reducing smoking initiation by 6.5% among 15–16-year-olds, four years on from the start of the intervention, and 25.6% of the students in the program were less likely to report having ever smoked compared to those who did not take part [27,28,29]. By employing “Implementation Intentions”, the program supports young people in resisting tobacco products offers by increasing their motivation to abstain from smoking and then helping them develop specific personalized plans/strategies to act on that motivation, in situations where they are offered tobacco products [30,31].

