Our program will utilize the “Teach-the-Teacher” model, originally developed by the IPCRG, and adapted to train the country MTs to approach teachers and students, and adapt and “Implementation Intentions” to the Greek context [42,43]. This approach could support sustainability and scalability, empowering teachers to educate other teachers in the future so that more school teachers can start implementing the INTENT program, eliminating the need for constant external support. Studies have suggested that teacher-led, school-based prevention programs seem effective in preventing adolescents from smoking initiation and strengthening their refusal skills, especially when they are interactive, age-appropriate, and integrated into regular school activities [3,42,55,57]. Building on this, our intervention will be structured in two concise sessions, designed to fit the Greek academic calendar and avoid disruptions from holidays and exams due to appropriate planning. Moreover, we will utilize open digital platforms like Google Classroom to provide continuous support to teachers. On the other hand, our intervention could also empower teachers by improving their knowledge, attitudes and confidence towards preventing and reducing smoking among adolescents. These factors have been consistently highlighted by systematic reviews and meta-analyses to improve the delivery of health interventions in the classroom through structured training [47,55,57,58]. This multifaceted design may also provide broader psychosocial benefits, such as increased refusal confidence and reduced social isolation through group discussions, consistent with meta-analyses showing that “Implementation Intentions” strengthen behavioral intentions in adolescents [47,55,59]. Additionally, we anticipate that these improvements in participants’ knowledge, attitudes, and likelihood of smoking could be measured through the RE-AIM framework to determine reach, effectiveness, adoption, implementation, and maintenance.

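### Refusal capacity, one of the two parts of the program's stated mechanism, is described as measured at follow-up only, so its change cannot be estimated

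*Protocol article*

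**What the plan says.** Students fill in questionnaires "at two timepoints, baseline (before the delivery of the sessions) and follow-up (after the delivery of the two sessions"). Section 2.5.1 gives the baseline content in two lists. The general list opens: "The baseline questionnaire will assess socio-demographic characteristics, family environment, cigarette use, e-cigarette use, nicotine pouch use, exposure to secondhand smoke", and goes on to air pollution, respiratory symptoms and productivity. The tobacco list covers ever-use, past-30-day use, "tobacco offers received from peers, susceptibility and curiosity towards tobacco use, intentions (to initiate smoking, quit smoking or try smoking"), and perceived harm of three product categories. Neither list has an item on refusal skill, refusal confidence or how a student responds to an offer.

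On the follow-up questionnaire, the section says: "This questionnaire will reassess tobacco use and susceptibility measures to allow for pre- and post-intervention comparisons". It then adds: "There will be a section which will assess refusal capacity, the perceived usefulness of the two sessions", along with how students react when offered tobacco.

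The Introduction says that the program works by raising motivation to abstain and then "helping them develop specific personalized plans/strategies to act on that motivation, in situations where they are offered tobacco products". The Discussion says that the design may bring wider psychosocial benefits, among them "increased refusal confidence and reduced social isolation through group discussions". Section 2.7 plans paired t-tests with Cohen's d for change. Section 3.1 acknowledges that there is no control group.

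**The concern.** The Personal Plans are refusal plans. The Abstract describes If-Then plans as plans for turning down a cigarette. Session 1 closes with a written exercise on refusal tactics and a first Personal Plan, and Table 3 gives refusing cigarettes as the purpose of that plan. Refusal capacity is therefore close to what the teachers deliver, and the Discussion raises the possibility that it will rise.

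A rise is a statement about change, and one measurement cannot show change. The study also shortens the UK program from eight sessions to two. If susceptibility does not move, the team will want to know whether refusal skill failed to improve, or improved without affecting susceptibility. The measures as described cannot separate these two explanations. An analysis plan cannot repair this later, because a baseline value that was never collected cannot be recovered.

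**Working it through.** The protocol gives no figure for this point, so the first check is a comparison of the described content by timepoint.

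| Construct | Baseline | Follow-up | Paired change possible? |
|---|---|---|---|
| Tobacco use | listed | reassessed | yes |
| Susceptibility | listed | reassessed | yes |
| Refusal capacity | not listed | listed | no |
| Reactions to tobacco offers | not listed (only offers received) | listed | no |
| Perceived usefulness of the sessions | cannot apply | listed | not needed |

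**Which questionnaire holds the refusal section.** The sentence does not name the instrument. It directly follows the description of the follow-up questionnaire, and the same section asks about the usefulness of the two sessions, which can be judged only after they have been held. Follow-up only is the natural reading. No other part of the article mentions a baseline refusal measure.

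**What can be computed.** A paired t-test and its Cohen's d need two values per student. Refusal capacity has 0 at baseline and 1 at follow-up, so there are 0 pairs. There is no control group, so no between-group contrast can take the place of the missing baseline.

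**What adding the items would give.** This figure only illustrates the gain; the point does not depend on it.

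- Inputs from the article: about 480 students (2.2) and 20% attrition (2.6). Pairs: 480 × 0.8 = 384.
- Assumed: every one of the 480 enters the evaluation, and the design effect (DEFF) for clustering is 1.3 to 1.75. The article gives no intraclass correlation or design effect.
- Two-sided alpha 0.05 and power 0.80 give 1.96 + 0.84 = 2.80. Detectable d, in standard deviations of the change score, is 2.80 / √(pairs / DEFF).
- DEFF 1.3: 384 / 1.3 = 295.4, and 2.80 / √295.4 = 0.163.
- DEFF 1.75: 384 / 1.75 = 219.4, and 2.80 / √219.4 = 0.189.
- With the 450 students of 2.6, pairs are 450 × 0.8 = 360, and the same formula gives 0.168 and 0.195.

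**The case against.** The strongest reply is that the protocol never promises an estimate of change in refusal capacity. The research question in the Introduction asks about susceptibility and related attitudes. Use and susceptibility are measured twice. Refusal capacity sits beside perceived usefulness, as part of a post-session evaluation in an exploratory pilot. This stands, and it limits the weight of the point: no stated aim becomes unanswerable.

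A second reply is that the article condenses questionnaires that are not shown, so an unlisted baseline item cannot be excluded. This also stands. But the baseline list is detailed and the statement of what is repeated is specific. If refusal is measured at baseline, 2.5.1 should say so.

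A third reply is that a paired change without controls could not be credited to the program. That is true, and it applies equally to susceptibility.

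Some stronger readings are tempting and are not supported:

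- A reader might infer that the program's main mechanism goes unmeasured before and after. The Introduction names two parts, and the motivational side (intentions, susceptibility) is in the baseline list.
- A reader might infer that both sessions centre on refusal. Session 2 is about personal resilience, external influences and stress, although a Personal Plan is written again.
- A reader might infer that the Discussion predicts greater refusal confidence. It says only that the design may provide this, and it does not include refusal among the improvements it anticipates measuring through RE-AIM.
- A reader might infer that refusal capacity is the outcome most likely to move because initiation will be rare over the study period. The article gives no figure for either idea, and its stated target is susceptibility, not initiation alone.

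**Conclusion.** The point holds as a cheap improvement. On the article's description, change in refusal capacity and in reactions to offers cannot be estimated, and the possible gain in refusal confidence named in the Discussion cannot be examined quantitatively. The pre-post comparison of susceptibility is untouched.

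The conclusion rests on reading the refusal section as follow-up only and on the baseline lists being complete for this construct. The detectable d of about 0.16 to 0.19 rests on the assumed design effects, full entry of 480 students into the evaluation and 20% attrition. Students may decline the evaluation (2.2.3), so the true number of pairs could be lower and the detectable d larger.

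**What to change.** In 2.5.1, add to the baseline questionnaire the identical refusal-capacity items used at follow-up. Add the reaction-to-offers items too, either only for students who report having been offered tobacco or worded hypothetically so that all can answer. Keep perceived usefulness at follow-up only. In 2.7, list change in refusal capacity as a secondary, exploratory, uncontrolled pre-post outcome.

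If baseline collection is already complete, state instead that refusal capacity is described at follow-up only and draw no conclusion about improvement.

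The cost is a few items on questionnaires that 2.5 says are still to be developed. The downsides are a slightly longer baseline questionnaire and possible mild priming of students before Session 1.

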The aforementioned findings have important implications for smoking prevention programs in Greece and highlight the need for further exploration of tobacco control interventions in Greek schools. Therefore, the aim of this study protocol is to describe the cultural adaptation procedure and the proposed implementation and evaluation of the school-based “Implementation Intentions” program aimed at reducing TU susceptibility among Greek adolescents aged 13–16 in school settings. The specific research questions of this study are:To what extent is the Greek adaptation of the INTENT program associated with changes in tobacco use susceptibility and related attitudes among adolescents aged 13–16?How do key stakeholders, including teachers and a representative group of adolescents, perceive the feasibility, acceptability, and potential effectiveness of the INTENT program?”

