#### 2.4.2. Implementation Phase of the Study—Teachers Utilizing the Intervention at Their Classrooms (Phase IV)

The second phase of the intervention will be based on the deliverance of the “Implementation Intentions” intervention by the teachers at the schools. The implementation, as mentioned above, will be conducted in six different schools and will consist of two structured sessions (Table 3). Both sessions, each lasting two school hours (~90 min), will be delivered by trained teachers, scheduled approximately two months apart. MTs will oversee all sessions and assist teachers where needed. In the first session, teachers will introduce our intervention to students. Introducing our intervention, teachers will explain that through this program students will have the opportunity to explore the factors in their life that may influence them to smoke. Teachers will highlight the fact that committing to do something by putting this commitment down on paper is much more likely to result in success, by creating a “Personal Plan (PP)”. This session includes interactive conversations with students addressing myths and truths about TU and the long-term effects of initiating smoking, as well as quizzes regarding TU. The first session will conclude with a written exercise outlining each student’s refusal tactics, followed by the development of their Personal Plans (PPs). The second session aims to strengthen students’ personal resilience and highlight the complexity of external influences on their decision to remain smoke-free. Moreover, teachers will examine what students can recall from the previous lecture. Students will be informed about how smoking interplays with stress and once again, they will create their PP. It should be noted that both quantitative and qualitative data will be collected by the MTs, before, during and after the intervention.

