### 2.7. Data Analysis

Quantitative data will be analyzed using the IBM SPSS 29 program. Descriptive statistics will summarize participant characteristics and engagement metrics. Paired *t*-tests and regression analyses will evaluate changes in the tobacco-related behaviors and attitudes of the participating students. Multiple linear regression analysis will be used to assess the strength and direction of the relationships between variables across the implementation period. As this study is exploratory, *p*-values will be interpreted alongside effect sizes and 95% confidence intervals. These will be the primary indicators of the strength and precision of the potential associations found. Specifically, Cohen’s d will be reported for paired *t*-tests, and standardized beta coefficients (β) for regression analyses. Statistical significance will be set to *p* < 0.05.

Interviews/focus groups will be audio-recorded, transcribed, and analyzed thematically by the MTs. More specifically, qualitative data will be analyzed using Braun and Clarke’s six-step framework for thematic analysis (Braun and Clarke) [50]. This involves transcribing and thematically analyzing the interviews and focus groups. First, the process involves verbatim transcription of audio-recorded interviews and focus groups, followed by multiple readings to understand the content. The transcripts will then be coded inductively (allowing themes to emerge) and deductively (focusing on study-specific aspects like adherence and quality of life). Codes will be grouped into categories, then refined into broader themes and subthemes. Finally, these themes will be presented with supporting quotes, and the qualitative findings will be triangulated with quantitative data to identify convergence or divergence between measurable outcomes and self-reported experiences [51].

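### The printed student scale has hedged end anchors, so firm and tentative refusal share the lowest score; this floor can attenuate the pre-post change in susceptibility but does not abolish it

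*Protocol article*

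**What the plan says.** The first research question in the Introduction asks how far the adapted program is "associated with changes in tobacco use susceptibility and related attitudes among adolescents aged 13–16". Section 2.5.1 lists susceptibility, curiosity and intentions among the student measures and says of the follow-up instrument: "This questionnaire will reassess tobacco use and susceptibility measures to allow for pre- and post-intervention comparisons". For both student questionnaires it fixes the response format: "students will rate their agreement on a four-point Likert scale, ranging from 1 (probably not) to 4 (probably yes". Only points 1 and 4 are given labels.

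Section 2.5 gives another format for the study's questionnaires: "close-ended questions will be either Likert-type (rated 1-almost never to 5-almost always) or dichotomous (yes or no". On scoring it says: "Each question will yield a score, and these scores will be summed for a total".

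On the analysis of change, section 2.7 names paired t-tests and says that "regression analyses will evaluate changes in the tobacco-related behaviors and attitudes of the participating students". Cohen's d is to be reported for the paired tests, and effect sizes with confidence intervals are to carry the interpretation.

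On the mechanism, section 2.4.2 has teachers tell students that "committing to do something by putting this commitment down on paper is much more likely to result in success". Students write a Personal Plan in each of the two sessions.

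**The concern.** The intervention works through a written commitment to refuse, so turning a tentative no into a firm one is a plausible part of its benefit. A scale whose lowest option is *probably not* gives that step no room. A student already certain has to tick the same box as one who is leaning towards refusal.

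Many students may start at or near that box. The Introduction puts smoking prevalence at 15% among Greek 15–16 year olds and places the emphasis of prevention on those who have never smoked. The share at the lowest score is not given, however.

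At stake is the estimate that answers the first research question. A floor in the items passes into the summed score, the paired mean difference and Cohen's d. Later analysis cannot recover a distinction that the response options never recorded.

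**Working it through.** The plan gives no figure of its own on this point, so there is none to reproduce. The check has two parts.

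**1. The two formats side by side**

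| Place | Format | Firm end? |
|---|---|---|
| Section 2.5.1, both student questionnaires | 4 points, *probably not* to *probably yes* | No, at either end |
| Section 2.5, Likert-type items | 5 points, *almost never* to *almost always* | No, at either end |
| Section 2.5, dichotomous items | Yes or no | An unhedged no, but no grading of firmness |

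The first two formats cannot both hold for the same item. No section assigns the susceptibility or intention items to the yes/no format.

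**2. Size of the floor for one item**

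Input from section 2.5.1: lowest score 1 = *probably not*, highest score 4 = *probably yes*.

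Assumptions, not in the documents:
- True level T is 0 (firm no), 1 (*probably not*), 2, 3 or 4 (*probably yes*), with baseline shares p0 to p4.
- The recorded score is max(1, T).
- A fraction q of students at every level above 0 moves one step down.

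Formulas:
- True mean change = −q × (p1 + p2 + p3 + p4)
- Recorded mean change = −q × (p2 + p3 + p4)
- Share lost = 1 − recorded/true = p1/(1 − p0), which does not depend on q

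Results with q = 0.2:

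| Assumed baseline (p0, p1, p2, p3, p4) | True change | Recorded change | Share lost |
|---|---|---|---|
| 0, 0.30, 0.30, 0.25, 0.15 | −0.20 | −0.14 | 30% |
| 0, 0.50, 0.25, 0.15, 0.10 | −0.20 | −0.10 | 50% |
| 0, 0.70, 0.15, 0.10, 0.05 | −0.20 | −0.06 | 70% |
| 0.40, 0.30, 0.15, 0.10, 0.05 | −0.12 | −0.06 | 50% |

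With q = 0.1 or 0.3 the shares lost are the same. No scenario loses everything. For individual students, 1 to firm no scores 0, while 2, 3 or 4 down to 1 scores −1, −2 or −3.

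The fourth row also shows what a firm anchor would achieve. On the printed scale 0.40 + 0.30 = 70% of students sit at the floor at baseline. With a firm-no category, 40% still do.

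These percentages apply to the mean change. Cohen's d need not fall by the same percentage, because the spread of the change scores shrinks too.

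**The case against.** The strongest reply is that one summary sentence about an unseen questionnaire is being read too literally. It labels only two of four points. It is applied to whole questionnaires that also cover demographics and past-30-day use, which cannot be answered on such a scale. Exact item labels are often left to the instrument. This has weight: the sentence may be shorthand. But the article does state the end anchors, and followed as written they merge firm and tentative refusal. If they are shorthand, correcting the sentence takes one line.

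A second reply is that other measures escape the problem: use of tobacco products, reactions to offers, refusal capacity and the interviews. This is partly right. However, the refusal section ("There will be a section which will assess refusal capacity") is described only for the follow-up questionnaire, so no baseline for it is stated.

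A third reply is that scores are summed, so a student is at the floor of a total only by giving the lowest answer throughout. That is true of the share of students at the floor. It does not remove the attenuation: the mean change in a total is the sum of the item mean changes, so what each item loses, the total loses.

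Two stronger readings are tempting, and the documents do not support them.
- A reader might infer that the effect the program aims for scores as zero. That holds only for students already at 1. The stated aims are lower susceptibility and less initiation, and nothing limits the target to the step from a tentative to a firm no.
- A reader might infer a bias towards apparent harm, since students at the floor can only stay or rise. That depends on which movements are assumed. If 5% of students rise one point and another 5% fall one point from the higher categories, the recorded changes of +0.05 and −0.05 cancel.

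**Conclusion.** The point holds as a measurement weakness of partial effect. As printed, the student scale gives firm and tentative refusal the same lowest score, and the competing Likert format in section 2.5 has no firm end either. This can attenuate the pre-post change in the susceptibility, curiosity and intention items.

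The loss is about 30% to 70% of the mean single-item change under the assumed baselines. That range rests on assumed distributions, a uniform one-step downward movement and a literal reading of the printed labels. The true figure could lie outside it, because the article gives no baseline distribution. The documents establish no net direction of bias beyond attenuation.

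It merits correction even in an exploratory pilot, because it touches the outcome of the first research question and the lost distinction cannot be restored at analysis.

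**What to change.** - Reconcile sections 2.5 and 2.5.1, stating which response format applies to which items and giving all the labels.
- Before the baseline survey, label the susceptibility, curiosity and intention items 1 *definitely not*, 2 *probably not*, 3 *probably yes*, 4 *definitely yes*, identically at both surveys.
- Report the share of students answering *definitely not* to all susceptibility items, before and after, alongside the mean score.
- State that some floor remains: students already firm at baseline cannot score lower.

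The cost is a relabelling of response options in a questionnaire that the team develops itself, with no added items, time or participants. If baseline data have already been collected under the printed labels, changing them at follow-up alone would break the comparison. In that case keep the labels, report the share at the lowest score at baseline, and name the floor as a limitation.
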